### **Collaborating researchers:**

[name] [name], PhD. Department of Pharmacology and Pediatrics, Faculty of Medicine, Malaga University. Biomedical Research Institute of Malaga (IBIMA), Malaga, Spain. Unit of Pediatric Pulmonology, Malaga Regional Hospital, Malaga, Spain.

[name] [name]. Physiotherapist specialist in children chest physiotherapy. Department of Pharmacology and Pediatrics, Faculty of Medicine, Malaga University, Biomedical Research Institute of Malaga (IBIMA), Malaga, Spain.

[name] [name]. Professional musician and music teacher of children. Department of Pharmacology and Pediatrics, Faculty of Medicine, Malaga University. Biomedical Research Institute of Malaga (IBIMA), Malaga, Spain. Department of Education. Andalusian Government, Malaga, Spain.

**Objective:** To develop a strategy based on music therapy as adjunct to daily chest physiotherapy in children with cystic fibrosis and to evaluate its effects.

**Study design:** Interventional - randomized controlled trial. Single center: Unit of Pediatric Pulmonology, Malaga Regional Hospital.

**Disease or disorder under study:** Cystic fibrosis.

**Participants:** Children between ages of 2-17 from the Pediatric Pulmonology Unit at Malaga Regional Hospital. The sample size determined in each group is 13 participants. A total of 39 participants are necessary.

**Total study period:** Two years.

## BACKGROUND

Cystic fibrosis (CF), is a rare, chronic, multisystemic disease that greatly affects the quality of life. A progressive lung dysfunction and its clinical manifestations are found in 95% of patients (CFF, 2014). These clinical manifestations are mainly related to morbidity and mortality (Alexander et al, 2014, CFF, 2014). Thus, the decrease in lung capacity and its consequences contribute to a degeneration of lung tissue, being ultimately the lung transplantation the only solution (Prados et al, 2000, CFF, 2014). Therefore, it is essential to establish an adequate treatment that prevents the progression of the lung disease. Chest physiotherapy (CPT) is one of the main approaches used to improve airway clearance, being essential in the maintenance of pulmonary function in CF due to the excess of respiratory secretions in these patients (McIlwaine et al, 2014).

Chest physiotherapy treats bronchial obstruction through airway clearance techniques administration such as deep breathing, huffing, coughing, percussions or vibrations (Pisi and Chetta, 2009; Main et al, 2011; CFF, 2014). The CPT is prescribed daily, requiring a significant commitment of time and energy for children and family members, what complicates CPT adherence (Modi & Quittner, 2006) and reduces its benefits (Sabaté, 2003; Goodfellow et al. , 2015).

Music exerts a motivational role in chronic diseases leading to psycho-emotional improvement (Le Roux et al, 2007). Music therapy (MT) interventions are usually part of integrative strategies to ameliorate some physical and/or psycho-emotional consequences in lung diseases, case of chronic obstructive pulmonary disease (Bausewein et al, 2013; Panigrahi et al, 2014). Patients reach emotional positive states reducing anxiety and depression with MT (Canga et al, 2015). In this sense, there are few music therapy interventions in CF (Goldbeck et al, 2014; Irons et al, 2014). Recently, it has been described that a carefully selected motivational music can lead to positive affective response during exercise in CF children aged from 8 to 18 (Calik-Kutukcu et al, 2016). There is only one study in CF infants and children under 2 years of age where, an appropriate music created specifically for CPT, helps to establish CPT as a routine by converting it into a positive experience (Grasso et al, 2000 ).

## HYPOTHESIS

The adherence in chronic disease treatment is very low (Sabaté, 2003), being the CPT adherence in CF less than 50 % (Goodfellow et al, 2015). To improve airway clearance in CF patients, there is no therapeutic alternative to CPT, in any case, it has to be combined with physical exercise (Kriemler et al, 2016). Motivation is the best way to optimize treatment adherence (Smith et al, 2010) and the use of carefully selected music during CPT (Grasso et al, 2000) or physical exercise (Calik-Kutukcu et al, 2016) in CF

patients can lead to a positive affective response that could be translated into a improvement in adherence (Smith et al, 2010) and therefore in airway clearance that could maintain the lung function and improve the children's and family member's quality of life.

Baseline hypothesis: Significant differences are expected in chest physiotherapy enjoyment and perception, adherence to daily chest physiotherapy, pulmonary symptomatology and quality of life between participants that use specific composed music as an adjunct to chest physiotherapy routine (intervention group), commercial music as an adjunct to chest physiotherapy routine (control group with music), or no music (control group without music).

## OBJECTIVES

### Main objective:

To develop a strategy based on music therapy as adjunct to daily chest physiotherapy in children with cystic fibrosis and to evaluate its effects. Instrumental music specifically composed, interpreted and compiled to cystic fibrosis children as an adjunct to chest physiotherapy routine will be used.

### Secondary objectives:

- To evaluate the effects of music therapy as an adjunct to chest physiotherapy on enjoyment, perception, adherence to daily chest physiotherapy of patients and family members.
- To evaluate the effects of music therapy as an adjunct to chest physiotherapy on pulmonary symptomatology and quality of life.

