**- Data collection:**

Demographic and clinical data will be collected in the case report formulary from each participant (Annex). Specifically: age, gender and respiratory infection exacerbations that requiring hospitalization.

These participants are controlled in the Pediatric Pulmonology Unit at Malaga Regional Hospital, where each child with cystic fibrosis has a detailed clinic history, being the clinical variables systematically included and the treatment updated. Therefore, the present study does not imply additional clinic information collection. Demographic and clinical information will be completed by Pediatricians during the usual follow-up.

In addition, participants will complete a baseline and 2 evaluation questionnaires during the trial-period in order to know children's and family members' chest physiotherapy perception. The questionnaires will be conducted about chest physiotherapy experiences to evaluate the evolution of their perceptions during the trial-period. These questionnaires are designed specifically to know evolution of CPT characteristics such as, enjoyment and perception or time or adherence to daily chest physiotherapy, after the use of music therapy as an adjunct to CPT (Grasso et al, 2000). The perception of pulmonary symptomatology and the impact on the quality of life will be also evaluate using a visual analog scale (VAS) to assess the magnitude of dyspnea in pulmonary diseases such as CF (Bausewein et al, 2007) and the revised cystic fibrosis quality of life questionnaire (Quittner et al, 2000), respectively.

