**- Study variables:**

- Demographics:
  - Age (quantitative variable) (unit: years)
  - Gender (qualitative, dichotomous variable) (male / female)
- Clinics:
  - Number of respiratory infection exacerbations that requiring hospitalization (quantitative variable)
  - Days of hospitalization per exacerbation (quantitative variable)
- Chest physiotherapy characteristics:
  - Use of activities to accompany the routine (qualitative, dichotomous variable) (yes /no)
  - Type of activities used to accompany the routine (toys, stories, music, radio, TV...) (qualitative variable)
- Chest physiotherapy adherence:
  - Routine frequency (quantitative variable)

- Number of times per day (quantitative variable)
- Interruptions (qualitative, dichotomous variable) (yes /no)
- Length per session (quantitative variable)
- Chest physiotherapy attitude:
  - Response to the routine using a Likert scale (-3 to +3): least enjoyment – neutral - most enjoyment (quantitative variable)
  - Feelings about the routine choosing 3 words to describe these feelings (qualitative variable)
- Perception of time taken to complete the chest physiotherapy:
  - Perception of being a long routine (qualitative, dichotomous variable) (yes /no)
  - Time that seems to need the routine (quantitative variable)
- About the music:
  - Music use frequency (quantitative variable)
  - Response to the use of music during routine using a Likert scale (-3 to +3): least enjoyment – neutral - most enjoyment (quantitative variable)
  - Usefulness of music during routine (qualitative, dichotomous variable) (yes /no)
  - How music has been useful (qualitative variable)
  - To continue using this music as an adjunct to the routine in the future (qualitative, dichotomous variable) (yes /no)
- Perception of pulmonary symptomatology and impact on quality of life:
  - Measurement of the symptoms of dyspnea using a dyspnea visual analog scale (VAS), being 1 no dyspnea and 7 maximal dyspnea.
  - Frequency of respiratory symptoms according to the revised quality of life questionnaire for cystic fibrosis during the previous 2 weeks: cough during the day and night, expectoration and type of expectoration, breathing difficulties, whistling sounds when breathing, and respiratory congestion.

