#### QUESTIONNAIRES:

☐ Chest physiotherapy characteristics:

- Use of activities to accompany the routine (yes /no)
- Type of activities used to accompany the routine (toys, stories, music, radio, TV...)

- ☐ Chest physiotherapy adherence:
  - Routine frequency
  - Number of times per day
  - Interruptions (yes /no)
  - Length per session
- ☐ Chest physiotherapy attitude:
  - Response to the routine using a Likert scale (-3 to +3): least enjoyment – neutral - most enjoyment
  - Feelings about the routine choosing 3 words to describe these feelings
- ☐ Perception of time taken to complete the chest physiotherapy:
  - Perception of being a long routine (yes /no)
  - Time that seems to need the routine
- ☐ About the music:
  - Music use frequency
  - Response to the use of music during routine using a Likert scale (-3 to +3): least enjoyment – neutral - most enjoyment
  - Usefulness of music during routine (yes /no)
  - How music has been useful
  - To continue using this music as an adjunct to the routine in the future (yes /no)
- ☐ Perception of pulmonary symptomatology and impact on quality of life:
  - Measurement of the symptoms of dyspnea using a dyspnea visual analog scale (VAS), being 1 no dyspnea and 7 maximal dyspnea ☐
  - Frequency of respiratory symptoms according to the revised quality of life questionnaire for cystic fibrosis during the previous 2 weeks:

always, often, sometimes, never

Coughing during the day..... ☐ ☐ ☐ ☐

Wake up at night because of coughing..... ☐ ☐ ☐ ☐

To expectorate (spit out the mucus)..... ☐ ☐ ☐ ☐

Mucus appearance: ☐ Watery ☐ Yellow/Transparent ☐ Yellow-Green ☐ Green/Bloody

☐ I do not know

Respiratory congestion..... ☐ ☐ ☐ ☐

Whistling sounds when breathing..... ☐ ☐ ☐ ☐

Breathing difficulties..... ☐ ☐ ☐ ☐

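### Quality of life is set as an outcome of its own, but only respiratory symptoms are collected, so no effect beyond symptoms can be concluded

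*Combined protocol and SAP*

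**What the plan says.** The second of the Secondary objectives is "To evaluate the effects of music therapy as an adjunct to chest physiotherapy on pulmonary symptomatology and quality of life". The Hypothesis expects group differences in "adherence to daily chest physiotherapy, pulmonary symptomatology and quality of life between participants that use specific composed music" and the comparison groups, and the Applicability section expects improvement in the same list. In all three places pulmonary symptoms and quality of life are two outcomes.

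The Data collection section pairs each with its own instrument. A visual analog scale for dyspnea serves symptoms, and quality of life is measured with "the revised cystic fibrosis quality of life questionnaire (Quittner et al, 2000), respectively".

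Under Study variables, what is taken from that questionnaire is "Frequency of respiratory symptoms according to the revised quality of life questionnaire for cystic fibrosis during the previous 2 weeks". The form in the annex, under the heading "Perception of pulmonary symptomatology and impact on quality of life", prints the same items.

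On adherence, the Hypothesis cites a background figure, "being the CPT adherence in CF less than 50" per cent. The study's own adherence variables are how often the routine is done, how many times a day, whether it is interrupted and how long a session lasts. Neither the questionnaire nor the case report form has a field for the prescribed number of sessions.

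**The concern.** An outcome that the plan names separately needs at least one measurement that can move independently of the other outcomes. If everything filed under quality of life is a respiratory symptom, a favourable result there is a second report of the symptom outcome. A report that followed the wording of the hypothesis and objective would then claim a benefit for which there are no data. Domains that were never asked about cannot be recovered at analysis.

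The adherence question is similar but weaker. The rationale speaks of adherence as a percentage, which implies a denominator, and the forms do not collect one.

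**Working it through.** The plan states no figure for quality of life or adherence. Its 13 per group is calculated for perceived time and does not bear on this point. The check is therefore mainly a comparison of sections.

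**Quality of life: what is promised and what is collected**

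| Place | Content |
|---|---|
| Hypothesis, Secondary objectives, Applicability | Symptoms and quality of life listed as separate outcomes; no instrument named |
| Data collection | Dyspnea scale for symptoms; revised CF questionnaire for quality of life |
| Study variables | From that questionnaire, respiratory symptom frequency only |
| Annex, Questionnaires | Six frequency items: day cough, night cough, expectoration, congestion, wheeze, breathing difficulty. One item on mucus appearance. One dyspnea scale |

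Count: 6 + 1 + 1 = 8 items under the heading, of which 0 concern anything other than respiratory symptoms.

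- The dyspnea item is "Measurement of the symptoms of dyspnea using a dyspnea visual analog scale (VAS), being 1 no dyspnea and 7 maximal dyspnea", which is a symptom rating.
- The item closest to an effect on daily life is "Wake up at night because of coughing", but Study variables classes it as night-time cough.
- No family quality-of-life item appears, although the rationale in the Hypothesis mentions family members.
- The variable list and the form agree with each other, so this is not a slip in one place. The Data collection section is the one that differs.

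**Adherence: what the missing denominator does**

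Share performed = sessions reported / sessions prescribed. The documents give no prescribed number per child; the Background says only that physiotherapy is prescribed daily. Assume 1, 2 or 3 prescribed sessions a day. A child who reports 7 sessions a week then has:

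- 1 a day: 7/7 = 100%
- 2 a day: 7/14 = 50%
- 3 a day: 7/21 = 33%

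The share therefore cannot be worked out for each child from the forms.

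For the comparison between groups, write reported sessions as Y = P × a, where P is the prescribed number and a the share performed. If P is constant during the trial, the change in Y is P × (change in a). A difference in P alone, with no change in a, produces no change in Y. What P does is scale the change, and a child already at a = 1 has no prescribed session left to gain.

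How far could P differ between arms by chance? Assume that half the children are prescribed 1 session a day and half 2, so the SD of P is 0.5. With 13 per arm:

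- SE of the difference in mean P = 0.5 × √(2/13) = 0.196
- 95% chance range = ±1.96 × 0.196 = ±0.38 sessions a day

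If all children have the same prescription, the range is zero. The documents do not say which applies, and without the field it could not be seen.

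**The case against.** **On quality of life.** The items come from a quality-of-life questionnaire, and respiratory symptoms are part of what it measures. That is correct, so it would go too far to say that nothing from a quality-of-life instrument is collected. It does not rescue the separate outcome, because the plan itself distinguishes symptoms from quality of life and gives each its own instrument. One could also argue that Data collection means the whole questionnaire. The variable list and the printed form are the operative texts for what is asked, and both show only the respiratory part. At the least, the three sections need to be reconciled.

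A reader might infer that symptom change will be published as a quality-of-life effect. The documents do not establish that, since Study variables labels the variable correctly as symptom frequency. Nor do the hypothesis, the objective or the Applicability section tie quality of life to a particular instrument; only Data collection does.

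**On adherence.** A reader might infer that adherence cannot be tested at all, or that an arm with heavier prescriptions would simply look more adherent. Neither follows. The hypothesis and objectives do not define adherence as a percentage of prescription, and the percentage in the rationale is a cited background figure. Allocation is random, the Intervention section plans no regimen changes, and the Statistical analysis section compares change over time between groups with baseline as one of the repeated measures. A constant prescription difference mainly shifts the level, not the change. The documents also do not show that prescriptions differ between children. What stands is a limit on interpretation: reported frequency is a proxy that cannot be set against what was prescribed.

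**Conclusion.** The quality-of-life point holds in full. None of the eight items under that heading measures quality of life beyond respiratory symptoms, so the trial can conclude on symptoms only. This rests on reading the variable list and annexed form as the complete set of questions.

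The adherence point holds only as a secondary one. Change in reported frequency, interruptions and session length can be compared between groups, but adherence relative to each child's prescription cannot. The figures of 100%, 50% and 33%, and the chance range of ±0.38 sessions a day, rest on assumed prescriptions and illustrate the gap without estimating it.

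Neither outcome drives the sample size, so the matter does not threaten the main comparison. It should still be settled before the first baseline questionnaire is completed.

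**What to change.** 1. **Relabel the outcome.** Replace quality of life by respiratory symptoms (respiratory items of the revised CF questionnaire) in the Hypothesis, Secondary objectives, Data collection, Study variables, Applicability and annexed Questionnaires. The cost is wording only, and the trial gives up a claim that it could not support.
2. **Or collect the rest.** If versions suited to the 2-17 age range are available, ask the remaining domains at baseline and at the two later questionnaires. The downside is a longer questionnaire three times over. The documents give neither versions nor length, so the added burden cannot be judged from them, and relabelling is the better supported choice.
3. **Optional, for adherence.** Add one case report form field for prescribed sessions per day or week. The exclusion criteria already require a check that physiotherapy is prescribed, and Data collection says that the clinic history keeps treatment up to date, so the likely source is at hand. State the unit of routine frequency, which is not given, and analyse performed/prescribed sessions beside the raw frequency. The cost is one field per child and one line in the analysis section.

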## METHODOLOGY, TRIAL PLAN AND SCHEDULE

### METHODOLOGY

#### **- Study design:**

Interventional prospective study on pediatric cystic fibrosis patients. Randomized controlled trial.

#### **- Scope:**

Single center: Unit of Pediatric Pulmonology, Malaga Regional Hospital, Malaga, Spain.

**- Participants:**

Children from the Pediatric Pulmonology Unit at Malaga Regional Hospital who meet all of the following inclusion criteria and none of the exclusion criteria:

**- Inclusion criteria:**

- Diagnosis of cystic fibrosis based on international criteria (Aldana et al, 2011).
- Children between ages of 2-17.
- Undergoing periodic clinic visits in the cystic fibrosis Unit.
- Understanding the purpose of the study.
- To provide written informed consent.

**- Exclusion criteria:**

- Children without chest physiotherapy prescription.
- Children with severe hearing loss.
- Children at radiologic or clinical risk of pneumothorax or pneumomediastinum.
- Children with barotrauma in the month prior to entry in the study.
- Children with past history of massive or life-threatening haemoptysis.
- Transplant recipients or children awaiting a lung transplant.

Children / legal guardian must have understood the purpose of the study and express their agreement by signing the informed consent prior to the inclusion in the study (model attached).

**- Sample size:**

To calculate the sample size, the perception of time taken to complete the routine has been assumed as main variable. According to Grasso et al, (2000) where the control group values in this variable were  $0.2 \pm 10.2$  (mean  $\pm$  SD), considering these values as baseline, a power of 80 %, a confidence level of 95 %, and a similar variability at the end of the study, a difference of 8 minutes would be considered as statistically significant with a sample size of 13 subjects. A total of 39 participants are necessary.

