#### **- Statistical analysis:**

Statistical analysis will be performed using SPSS Software.

Initially a descriptive analysis of the study variables will be carried out, the values of the continuous variables will be summarized in a table where their corresponding means and standard deviation will be shown. The categorical variables will be presented in absolute and relative frequencies.

To compare qualitative measures Chi-square or Fisher tests will be used, and ANOVA or Kruskal-Wallis tests to quantitative.

To contrast the differences in the evolution of the variables between the different groups the multivariate analysis of variance test of repeated measures (MANOVA) will be applied with a factor between subjects (group) and a factor intra subjects (different moments of the intervention). Depending on the compliance of the sphericity condition, the Greenhouse-Geisser correction will be used. To contrast the differences between baseline and final measures in each group Wilcoxon test will be applied. To compare response to using music after the intervention into TG and PG, Mann–Whitney U test was used.

To compare response to using music after the intervention into TG and PG, Mann–Whitney U test will be used.

A significance of 5% ( $p < 0.05$ ) will be required to consider a difference as statistically significant.

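### Thirteen per group does not give the stated 80% power for an 8-minute difference between groups; the figure matches a one-sample or paired formula

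*Combined protocol and SAP*

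**What the plan says.** The Sample size section states that "the perception of time taken to complete the routine has been assumed as main variable". It takes a mean of 0.2 and SD of 10.2 from the control group of an earlier study of music with chest physiotherapy, "considering these values as baseline", and assumes "a similar variability at the end of the study". With 80% power and "a confidence level of 95" per cent, it concludes that "a difference of 8 minutes would be considered as statistically significant with a sample size of 13 subjects", and then gives a total of 39. The Participants line of the opening summary shows how 13 is used: "The sample size determined in each group is 13 participants".

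The Hypothesis section is about contrasts between the specially composed music, commercial music and no-music groups: "Significant differences are expected in chest physiotherapy enjoyment and perception, adherence to daily chest physiotherapy, pulmonary symptomatology and quality of life". The Statistical analysis section tests differences in evolution between groups by a repeated-measures analysis, with group as the between-subjects factor and time as the within-subjects factor. The baseline-to-final Wilcoxon test within each group is listed separately. The plan gives no formula, sidedness, within-child correlation, dropout allowance or multiplicity adjustment for the sample size.

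**The concern.** A sample size for one group's change, or for one mean against a fixed value, is half the size needed per group to compare two independent groups with the same SD and difference. The stated inputs give 13 under the first formula and 26 under the second. The wording about baseline values and end-of-study variability also reads as a before-and-after set-up. Multiplying 13 by three arms does not turn it into a between-group calculation.

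This calculation is the only justification in the plan for enrolling 39 children. Anyone relying on the 80% would overestimate what a comparison of two arms can detect, and could give a non-significant result more weight than it deserves.

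**Working it through.** **Inputs from the plan:** SD 10.2; difference 8 minutes; power 80%; 5% significance; 13 per group; three groups. **Assumption:** two-sided testing, because the plan says only that p < 0.05 "will be required to consider a difference as statistically significant". The multiplier is 1.960 + 0.842 = 2.802.

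**1. Reproducing the 13.** One-sample or paired formula: n = (2.802 × 10.2 / 8)² = 12.76, rounded up to 13. This uses the normal approximation; the exact paired t-test at n = 13 has 74% power and would need 15.

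**2. Two independent groups.** n per group = 2 × 12.76 = 25.5, so 26 (27 by t-test), or 78 to 81 children in three groups. One-sided testing would need 21 per group. Taking the difference as 7.8 or 8.2, to allow for the 0.2 mean, gives 26.8 or 24.3 before rounding. A three-group ANOVA needs 25 per group if one mean differs by 8, or 33 if the means are 0, 4 and 8. None of these gives 13.

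**3. Power at 13 per group, with 10.2 as the SD of the analysed quantity.**
- Standard error of a difference: 10.2 × √(2/13) = 4.00. Noncentrality: 8 / 4.00 = 2.00.
- Pairwise two-sided t-test, 24 df: 48.4%. Normal approximation: 51.6%. Pooled error, 36 df: 49.4%. One-sided t-test: 62%.
- ANOVA, F with 2 and 36 df, noncentrality 13 × Σ(mean − grand mean)² / 10.2². Means 0, 0, 8: 13 × 42.67 / 104.04 = 5.33, power 49.5%. Means 0, 4, 8: 13 × 32 / 104.04 = 4.00, power 38.6%.
- Difference detectable with 80% power by the pairwise t-test: 11.7 minutes.
- Bonferroni over three pairs: 30% power by t-test.

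**4. The significance statement read literally.** An observed difference of exactly 8.0 minutes between two groups of 13 gives t = 8 / 4.00 = 2.00, p = 0.057 (24 df) or 0.053 (36 df). The smallest significant difference is 2.064 × 4.00 = 8.3 minutes (24 df), or 8.1 with pooled error.

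**5. If 10.2 is instead an SD at a single time.** Power then depends on the correlation r between baseline and follow-up. The change-score SD is 10.2 × √(2(1 − r)); the baseline-adjusted SD is 10.2 × √(1 − r²). The pairwise two-sided t-test at 13 per group gives:

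| r | Change score: SD, power | Baseline-adjusted: SD, power |
|---|---|---|
| 0.3 | 12.07, 37% | 9.73, 52% |
| 0.5 | 10.20, 48% | 8.83, 60% |
| 0.7 | 7.90, 70% | 7.28, 76% |

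For these analyses, 80% power needs a correlation above about 0.7.

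**6. The planned group-by-time test.** Assume equal correlation r between all three questionnaires and an 8-minute effect at both follow-ups. The interaction F has 4 and 72 df and noncentrality 13 × (2/3) × Σ(mean − grand mean)² / (10.2²(1 − r)). For follow-up means 0, 4, 8 and 0, 0, 8 respectively, power is 29% and 38% at r = 0.3, 40% and 52% at 0.5, 62% and 77% at 0.7, and 82% and 92% at 0.8.

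**The case against.** The strongest defence is that 48% is not the power of the planned analysis. It belongs to one unadjusted comparison of two arms, with 10.2 as the SD of whatever is analysed. The plan has a baseline and two follow-up questionnaires and names a repeated-measures test, whose power rises with the within-child correlation and passes 80% at 0.8. This stands. A reader might infer that the whole trial has a coin-flip chance of detecting 8 minutes, but the documents do not fix the correlation and so do not support that. Equally, they give no correlation on which the 80% could rest.

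A second defence concerns where 13 came from. The plan names no formula, so the one-sample origin is an inference. A two-group comparison adjusted for baseline at a correlation of 0.7 gives 25.52 × (1 − 0.49) = 13.0 per group. Averaging both follow-ups with baseline adjustment at 0.5 gives 25.52 × 0.5 = 12.8. So 13 cannot be said to arise in only one way. However, the plan describes neither calculation and specifies no baseline adjustment, while its wording about baseline and end-of-study variability fits the paired reading.

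Third, the meaning of 10.2 is uncertain. A mean of 0.2, set against a routine of about 40 minutes, suggests that it may already be a change or difference. If so, the correlation table does not apply and the results in step 3 do. The cited study is not available to settle this, so both readings are shown.

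**Conclusion.** Wrong as written. On the stated inputs, 13 per group does not give 80% power for an 8-minute difference between groups, and an observed 8-minute difference between two groups would narrowly miss significance at the SD assumed. The error does not depend on knowing which formula was used.

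The size depends on what 10.2 measures. If it is the SD of the analysed quantity, power is about 48% for one unadjusted pairwise two-sided t-test and 39–50% for a three-group ANOVA. If it is a single-time SD, power by change-score or baseline-adjusted t-test runs from about 37% to 76% over correlations of 0.3 to 0.7. All these figures assume 39 children with complete data; any dropout lowers them.

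Two further inferences are not supported. Nothing in the documents says that 39 was set by feasibility; the plan presents it as the result of the calculation. Nor does the plan contain a rule that a non-significant result would be taken to mean that music has no effect; that is a risk of misreading.

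**What to change.** In the Sample size section, and consistently in the Participants line of the summary, replace the claim for 8 minutes with 13 subjects by text such as:

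> With 13 participants per group, an unadjusted pairwise two-sided 5% t-test (SD of the analysed quantity 10.2) has about 48% power for an 8-minute between-group difference and 80% power for 11.7 minutes; 8 minutes at 80% power would need 26–27 per group. Power of the repeated-measures analysis depends on the within-child correlation. If 10.2 is a single-time SD, a change-score or baseline-adjusted t-test has about 37–52% power at a correlation of 0.3, 48–60% at 0.5 and 70–76% at 0.7.

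State whether 10.2 is the SD of a change or of a single measurement; the sponsor can check this in the cited study. In the Statistical analysis section, add that between-group differences will be reported with 95% confidence intervals (half-width 2.064 × 4.00, about 8.3 minutes, under the same assumptions as the 48%). Do not give feasibility as the reason for 39 unless the sponsor confirms it.

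The cost is wording only: no extra patients, visits or procedures. The stated power becomes less favourable. Enrolling 26–27 per group would be a separate decision for the sponsor.
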